**Abstract**

**Objectives:** The aim of this study is to evaluate the quality of care (QOC) of the Hospital Authority’s (HA) patient empowerment programme (PEP) programme using an evidence-based structured and comprehensive evaluation framework to identify areas for quality enhancement.

**Design, Setting and Subjects:** A longitudinal study will be conducted using the Action Learning and Audit Spiral methodologies to measure whether the target standard of care intended by the PEP programme is achieved. Each PEP participating clinic and non-government organization (NGO) will be invited to complete a structured evaluation questionnaire. The data of all patients who have enrolled into the PEP for more than one year will be included in the evaluation on the process and outcomes of care. To determine a difference of programme performance and impact between group (PEP participants and non-participants), cohort study would be adopted. A cohort includes all eligible DM patients under care of HA GOPC at 1 Sep 2009 will be followed up on the clinical outcomes including HbA1c, blood pressure, lipids, and complications rates. To evaluate the effect of PEP on patient-reported outcomes, 550 participants, as well as 550 of those who have not participated in the PEP, will be recruited from each cluster and followed up by telephone to evaluate the effect of the programme on quality of life (QOL), patient enablement, global rating of change in health condition and private service utilization at baseline, 6, 12, 36 and 60 months after enrolment. Data on the process of care will be retrieved from the HA medical records. The cost effectiveness analysis (CEA) by mathematical modeling will be carried out by using cost and clinical outcome data provided by the HA, as well as quality-of-life and private service utilization cost data collected by the telephone surveys.

**Main Outcome Measures:** The primary outcomes are the proportion of participants who have received the planned process of care and achieved the target HbA1c and blood pressure levels.

**Data Analysis:** Descriptive statistics on proportions meeting the QOC criteria will be calculated. The changes in clinical, service, and patient reported outcomes at 6 and 12 months will assessed by paired sample t-test for each audit cycle. The audit cycle will be repeated annually over a period of 5 years.

**Results:** The QOC of the PEP programme will be determined. Areas of deficiency and possible areas for quality enhancement will be identified.

**Conclusion:** The results of this study will provide empirical evidence on whether the HA’s PEP programme can enhance QOC for patients with diabetes mellitus (DM) or hypertension (HT). The information will be used to guide service planning and policy decision making.

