# Background

Diabetes mellitus (DM) and hypertension (HT) are major causes of morbidity and among the top 10 causes of deaths in Hong Kong in 2008 (Department of Health 2009). The Hospital Authority (HA) has initiated service improvement through introducing the patient empowerment programme (PEP) to improve the quality of care (QOC) for DM and HT patients. The evaluation on the QOC is an essential part of the programme in order to inform future policy. The Family Medicine Unit (FMU) of the University of Hong Kong (HKU) has been appointed by the HA to carry out the evaluation of the QOC of the programme.

The PEP programme invites non-Government organizations (NGO) with experience in community medical service and education to deliver empowerment sessions to enhance patients’ disease specific knowledge and self-management skills, self-efficacy and lifestyle modification. Eligible patients who are ambulatory, have stable mental and emotional conditions, and follow up at general outpatients clinics (GOPC) and family medicine specialist clinics (FMSC) regularly will be recruited for the PEP programme. Enrolled patients will receive generic and disease specific PEP sessions provided by the NGO. Patients will be excluded if they have severe heart failure, end stage renal failure (ESRF) or advanced eye diseases, are unable to understand or communicate in Chinese language, or refuse to give consent.

Studies have found that patient empowerment programmes are effective, especially those that include active patient involvement (Lorig and Holman 2003), in improving outcomes and are somewhat cost-effective. Although more studies would be needed to determine long-term benefits and the cost-effectiveness in both hard and soft indicators (i.e. health care utilization costs vs. less tangible measures of outcome, including quality of life (QOL) and self efficacy. Two trials in Hong Kong indicated the empowerment approach was applicable to the Hong Kong Chinese population (Chan, Chan et al. 2007; Siu, Chan et al. 2007).

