## Hypotheses

The following hypotheses will be tested:

1. The criteria on structure and process should be achieved by all participating clinics and NGO;
2. More patients with DM will achieve the target HbA1c after 12, 24, 36 and 48 months in the PEP programme;
3. More patients with HT or DM will achieve the target blood pressure levels after 12, 24, 36 and 48 months in the PEP programme;
4. In longer terms, HT/ DM patients will have reduced cardiovascular risks and fewer complications;
5. Patients should report an improvement in quality of life (QOL), enablement and overall health condition after the PEP programme;
6. Patients who take part in PEP programme should not have any increase in service utilization rates.

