## Subjects

All patients who have been enrolled into the PEP programme will be included in the evaluation on process of care for each audit cycle; whereas all enrolled subjects who have been recruited for more than 12 months in the programme will be included in the evaluation on the clinical outcomes of care for each audit cycle.

To determine a difference of programme performance and impact between group (PEP participants and non-participants). A cohort of all eligible DM patients under care of HA GOPC at 1 Sep 2009 would be included for the monitoring of the changes in clinical and service utilization outcomes from Sep 2009 to Sept 2015.

550 patients who have enrolled into the PEP and 550 who have not taken part in the PEP will be invited in person from the general outpatient clinics by trained research assistants at the beginning of each evaluation cycle to take part in a telephone survey on patient reported outcomes for each cluster and written consent will be obtained (appendix A). All subjects who have given consent to the telephone follow-up survey will be interviewed by telephone within four weeks, at 6, 12, 36 and 60 months from recruitment to answer the SF-12 Health Survey on quality of life (QOL), the patient enablement Instrument, the Global Rating Scale (GRS) change in health, and a structured questionnaire on private service utilization rates.

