## Outcome measures

**Primary**

- The proportion of clinics/NGO that have satisfied each of the set structure criteria.
- The proportion of patients who have complied with the criterion process of care.
- The proportion of DM patients who have achieved a HbA1c level <7%.
- The proportion of HT/ DM patients who have achieved the target blood pressure.
- The estimated 10-year cardiovascular disease risk.

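### For clinical and HA-service outcomes the only between-group cohort is diabetic GOPC patients, so the effectiveness claim for hypertension-only and FMSC participants has no non-PEP comparator

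*Protocol*

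**What the plan says.** The Abstract and the Subjects section define the comparison cohort in nearly the same terms. The Abstract has "A cohort includes all eligible DM patients under care of HA GOPC at 1 Sep 2009", and Subjects has "A cohort of all eligible DM patients under care of HA GOPC at 1 Sep 2009 would be included", followed from September 2009 to September 2015 for clinical and service-utilisation outcomes. Subjects gives its purpose as "To determine a difference of programme performance and impact between group (PEP participants and non-participants". No other between-group cohort is described for these outcomes.

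The programme and its claims are wider:

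- Background says that PEP was introduced "to improve the quality of care (QOC) for DM and HT patients", and that eligible regular attenders at "general outpatients clinics (GOPC) and family medicine specialist clinics (FMSC) regularly will be recruited for the PEP programme".
- Hypothesis 3 reads "More patients with HT or DM will achieve the target blood pressure levels", and hypothesis 4 (cardiovascular risk and complications) also names both diseases.
- One primary outcome is "The proportion of HT/ DM patients who have achieved the target blood pressure".
- The Abstract's conclusion promises evidence on whether PEP "can enhance QOC for patients with diabetes mellitus (DM) or hypertension (HT"). Item 3 under Implications promises effectiveness information for both diseases to guide policy.

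Under Data analysis, item 2 is a paired t-test of change after PEP. Item 3 is an independent t-test or chi-square test of PEP patients against controls, and it defines neither group.

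**The concern.** The population in which a PEP effect can be estimated against non-participants is narrower than the population about which the Protocol intends to conclude. A participant with hypertension but no diabetes, or one followed at an FMSC, counts towards the hypotheses and the programme-wide outcomes but lies outside the one cohort that supplies non-participants.

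For such patients the only planned inference is change from their own baseline. They are under regular follow-up in any case, so changes in prescribing, guidelines or routine clinic care over the same years would be counted as programme effect. The findings are meant to inform policy for both diseases, so a reader of the final report could take an uncontrolled HT result to be as strong as the controlled DM result.

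This is more than a detail for an analysis plan. If records of HT non-participants are never extracted, no later analysis can supply the comparison.

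**Working it through.** The Protocol states no figure on this point. Its one sample-size calculation concerns quality of life in the telephone survey and is unaffected. The check is a comparison of population definitions.

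**Step 1. Does PEP include HT-only patients?** The Protocol does not say so outright, but it follows from the wording. Hypothesis 2 and the HbA1c outcome are confined to DM, whereas hypothesis 3 and the blood pressure outcome are widened to HT. Appendix B item 10 asks for disease toolkits on both DM and HT.

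**Step 2. Which outcomes have a non-PEP comparator, and for whom?**

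| Outcome | Population the plan attaches | DM at GOPC | HT-only | FMSC |
|---|---|---|---|---|
| HbA1c below 7% (primary) | DM | yes | not applicable | none |
| Target blood pressure (primary) | HT/DM | yes | none | none |
| 10-year CVD risk (primary) | not named in the outcome list; hypothesis 4 names HT/DM | yes | none | none |
| LDL, BMI, cardiovascular and renal complications (secondary) | not named in the outcome list; hypothesis 4 names HT/DM for complications | yes | none | none |
| GOPC, SOPC, A&E and hospital attendance (secondary) | hypothesis 6: PEP patients | yes | none | none |
| SF-12v2, PEI, GRS, private service use (telephone survey) | 550 PEP and 550 non-PEP | yes | yes, disease mix unstated | both groups are recruited at GOPCs |

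The *yes* entries in the first five rows come from the DM GOPC cohort. Those in the last row come from the survey's non-participants, who are not restricted to DM.

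**Step 3. What analysis is left where the table says none?** Subjects places all those enrolled for more than 12 months in the clinical-outcome evaluation, whatever their disease. For patients outside the DM GOPC cohort the remaining test of programme effect is item 2, the paired comparison. It estimates PEP effect plus secular change plus the effect of continuing routine care, and contains nothing to subtract the last two.

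**Step 4. Does item 3 mix diseases?** Let h be the HT-only share of the PEP side of item 3, and d the difference in blood pressure control rate between HT-only and DM patients. With DM-only controls and no PEP effect, the expected difference between groups from disease mix is h × d. If both sides are drawn from the DM GOPC cohort, h = 0 and the difference is 0 × d = 0. If the PEP side were all enrollees, h would be above zero. The Protocol gives neither h nor d, so no magnitude can be derived from it.

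**The case against.** The strongest reply is that the HT part of the study is a declared audit. The Methods compare results with set standards, hypothesis 3 is worded as change after time in the programme, and the primary outcomes are proportions meeting a criterion. On this view, confining the controlled cohort to DM is a legitimate choice of scope. That holds for the audit aims. It does not cover the effectiveness and policy statements in the Abstract's conclusion and under Implications, which name HT beside DM without saying that the evidence differs in kind.

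Two limits on the concern also stand. Quality of life, enablement, global rating and private service use have non-participant comparators not restricted to DM. The DM part of the blood pressure outcome is controlled within the cohort, including DM patients who also have HT.

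A reader might infer that item 3 compares a mixed DM and HT PEP group with diabetic controls. The documents do not support that as a statement of the plan. The cohort is introduced to compare participants with non-participants, so its natural reading is a single DM GOPC cohort supplying both groups, with no disease-mix difference. What remains is that item 3 does not say this, while Subjects elsewhere refers to all enrolled patients.

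A reader might also infer that the HT before-after result is bound to improve through regression to the mean. The eligibility text in Background lists no blood pressure or HbA1c threshold for entry, so selection on high values is not shown.

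**Conclusion.** The concern holds in limited form. For clinical and HA-service-utilisation outcomes, HT-only and FMSC participants have no non-PEP comparator, and their results rest on a paired change that cannot isolate a PEP effect. Two of the five primary outcomes are affected for HT-only patients: blood pressure directly, and 10-year cardiovascular risk through hypothesis 4. For FMSC participants with DM, HbA1c is affected too.

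The conclusion assumes that PEP enrols patients with HT and no DM, which the wording implies without stating. It does not depend on any assumed rates, and no bias in percentage points can be attached to it. Secular trend is a real possibility, but its direction and size are unknown. The comparison within the DM GOPC cohort is not impugned on this ground. The point deserves correction because it decides which patients the effectiveness conclusion may cover.

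**What to change.** First, state in Data analysis item 3 that both groups are members of the DM GOPC cohort, participants against non-participants. This keeps HT-only and FMSC enrollees from being tested against DM controls, and costs one sentence.

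Then choose one of two courses:

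1. Extend the anonymised CMS extract to eligible HT non-participants, and to FMSC attenders, under the same eligibility rules. Run item 3 separately by disease stratum with like-for-like comparators. The cost is a broader data query and the added analyses.
2. Keep the cohort as it is. Limit the between-group effectiveness conclusion in the Abstract and under Implications to DM patients at GOPC, and report HT clinical and service results as uncontrolled before-after audit figures. This costs only wording, but leaves the study with no controlled claim for HT on these outcomes.

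The first course is preferable if policy for HT is to rest on the results. The second is adequate if HT is meant only as audit.

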# Background

Diabetes mellitus (DM) and hypertension (HT) are major causes of morbidity and among the top 10 causes of deaths in Hong Kong in 2008 (Department of Health 2009). The Hospital Authority (HA) has initiated service improvement through introducing the patient empowerment programme (PEP) to improve the quality of care (QOC) for DM and HT patients. The evaluation on the QOC is an essential part of the programme in order to inform future policy. The Family Medicine Unit (FMU) of the University of Hong Kong (HKU) has been appointed by the HA to carry out the evaluation of the QOC of the programme.

The PEP programme invites non-Government organizations (NGO) with experience in community medical service and education to deliver empowerment sessions to enhance patients’ disease specific knowledge and self-management skills, self-efficacy and lifestyle modification. Eligible patients who are ambulatory, have stable mental and emotional conditions, and follow up at general outpatients clinics (GOPC) and family medicine specialist clinics (FMSC) regularly will be recruited for the PEP programme. Enrolled patients will receive generic and disease specific PEP sessions provided by the NGO. Patients will be excluded if they have severe heart failure, end stage renal failure (ESRF) or advanced eye diseases, are unable to understand or communicate in Chinese language, or refuse to give consent.

Studies have found that patient empowerment programmes are effective, especially those that include active patient involvement (Lorig and Holman 2003), in improving outcomes and are somewhat cost-effective. Although more studies would be needed to determine long-term benefits and the cost-effectiveness in both hard and soft indicators (i.e. health care utilization costs vs. less tangible measures of outcome, including quality of life (QOL) and self efficacy. Two trials in Hong Kong indicated the empowerment approach was applicable to the Hong Kong Chinese population (Chan, Chan et al. 2007; Siu, Chan et al. 2007).

## Aim of Study

The aim of this study is to evaluate the quality of care (QOC) of the PEP programme using a structured and comprehensive evaluation framework that is evidence based, and to identify areas for quality enhancement.

## Hypotheses

The following hypotheses will be tested:

1. The criteria on structure and process should be achieved by all participating clinics and NGO;
2. More patients with DM will achieve the target HbA1c after 12, 24, 36 and 48 months in the PEP programme;
3. More patients with HT or DM will achieve the target blood pressure levels after 12, 24, 36 and 48 months in the PEP programme;
4. In longer terms, HT/ DM patients will have reduced cardiovascular risks and fewer complications;
5. Patients should report an improvement in quality of life (QOL), enablement and overall health condition after the PEP programme;
6. Patients who take part in PEP programme should not have any increase in service utilization rates.

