## Data analysis

1. Descriptive statistics on standard of care will be calculated, including percentage of centers meeting each structure criterion, percentage of subjects enrolled, dropped out, completion of the programme, receiving criterion process, investigations and referral per protocol, and percentage of subjects achieving the criterion outcome.
2. The change in clinical, service, and patient reported outcomes after the PEP programme at baseline, 6, 12, 36 and 60 months will be compared by paired sample t-test. The audit cycle will be repeated annually over a period of 5 years.
3. Independent sample t-test or Chi square test as appropriate will be used to compare the clinical and service utilization outcomes between PEP patients and controls.
4. Independent sample t-test or Chi square test as appropriate will be used to compare the clinical and service utilization outcomes between results in achieved in different audit cycles.
5. Cost effectiveness analysis (CEA) by mathematical modeling will be carried out by using cost and clinical outcome data provided by the HA, as well as quality-of-life and private service utilization cost data collected by the telephone surveys.

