**Patients require special treatment:**

| **Data Required** | **Number of  patients** | **Time (in days) from problem recognition** |
| --- | --- | --- |
|
| Identified to have problem being given treatments per protocol |  |  |
| Referred for additional service |  |  |
| Refused additional service |  |  |

| **Time (Month)** | **Data required** |
| --- | --- |
| 0, 12, 24, 36 and 48 | **Clinical data** |
| HbA1c |
| Systolic BP |
| Diastolic BP |
| BMI |
| LDL-C |
| **Service utilization** (in the past 12 months) |
| Number of hospitalization |
| Number of A&E attendance |
| Number of GOPC consultation |
| Number of SOPC consultation |
| 0 and 6 months | **Patient reported** |
| Disease knowledge score |
| QoL score |
| PEI* |
| GRS* |

BP = Blood Pressure; BMI = Body Mass Index; LDL-C = Low density Lipoprotein Cholesterol; GOPC = General Outpatient Clinic; SOPC = Specialist Outpatient Clinic; KAP = Knowledge, Attitude and Practice.

*Measured at 6 months only.

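### The primary outcome list, the comparator and the clinical time points conflict between sections, so the protocol does not fix which contrast decides whether PEP works

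*Protocol*

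**What the plan says.** **Primary outcomes.** The Abstract states: "The primary outcomes are the proportion of participants who have received the planned process of care and achieved the target HbA1c and blood pressure levels". Read item by item, that is three outcomes: process of care, HbA1c and blood pressure. The primary list under Outcome measures has five. It also contains "The proportion of clinics/NGO that have satisfied each of the set structure criteria" and "The estimated 10-year cardiovascular disease risk".

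**Hypotheses.** Item 2 reads "More patients with DM will achieve the target HbA1c after 12, 24, 36 and 48 months in the PEP programme". Item 3 uses the same construction and the same four times for blood pressure in HT or DM patients. Neither names a comparator.

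**Tests.** Data analysis item 2 takes clinical, service and patient-reported outcomes together; their change "after the PEP programme at baseline, 6, 12, 36 and 60 months will be compared by paired sample t-test". Item 3 provides t-tests or chi-square tests "used to compare the clinical and service utilization outcomes between PEP patients and controls" and gives no time point. Item 4 compares audit cycles with each other. The Abstract's analysis paragraph has paired tests at 6 and 12 months only.

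**Data.** The Appendix C form schedules clinical data at months "0, 12, 24, 36 and 48".

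**Purpose of the cohort.** The Abstract and Subjects both set up a cohort of DM patients, defined on 1 September 2009, to show the difference in performance and impact between participants and non-participants.

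**The concern.** The sections answer three basic questions differently: which outcomes are primary, what they are compared with, and when. No section joins a primary outcome to one comparator and one time.

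The choice of comparator matters most. The proportion of PEP patients at target can rise after enrolment because patients enrol when control is poor and drift back (regression to the mean), or because care improves everywhere (secular trend). Either can produce a clear before-after gain with no difference from non-participants. The protocol leaves both comparisons in place and does not say which one tests hypotheses 2 and 3. Under Implications, the results are meant to inform policy on effectiveness, so an analyst who has seen the data should not be the one to choose.

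The time-point conflict is also practical: part of the planned testing has no scheduled data, and part of what is hypothesised has no matching paired test.

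**Working it through.** **1. Primary lists**

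| Outcome | Abstract | Outcome measures |
| --- | --- | --- |
| Structure criteria met | no | yes |
| Process of care | yes | yes |
| HbA1c target | yes | yes |
| Blood pressure target | yes | yes |
| 10-year CVD risk | no | yes |

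Three against five; two outcomes are primary in one place only.

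**2. Clinical follow-up times (months)**

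| Section | 6 | 12 | 24 | 36 | 48 | 60 |
| --- | --- | --- | --- | --- | --- | --- |
| Abstract, Data Analysis | x | x | | | | |
| Hypotheses 2 and 3 | | x | x | x | x | |
| Data analysis item 2 | x | x | | x | | x |
| Appendix C, clinical data | | x | x | x | x | |

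- Hypotheses and Appendix C agree with each other. The conflict is with the Abstract and item 2.
- In item 2 but not in Appendix C: 6 and 60 months, so no scheduled clinical data.
- In the hypotheses but not in item 2: 24 and 48 months, so no matching paired test.
- Common to all four rows: 12 months only. Data Collection also names baseline and 12 months for clinical data.
- The times in item 2 are those that Subjects, Data Collection and the secondary outcome list give for the telephone survey. Item 2 appears to have applied the patient-reported schedule to the clinical outcomes.

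**3. Comparators on offer.** Within-patient change (item 2), PEP versus controls (item 3), cycle versus cycle (item 4) and results against set standards (Methods). None is ranked for hypotheses 2 and 3.

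**4. The only error level in the protocol.** Sample size calculation gives a 95% confidence interval, 80% power and an effect of 0.3 SD on quality of life. With a two-sided 5% test, n per group = 2 × (1.960 + 0.842)² / 0.3² = 174.4, rounded up to 175, or 350 in total, as stated. Four losses of 25% give 175 / 0.75⁴ = 553 per group, close to the stated 550. The figure reproduces, but it concerns a secondary outcome and sets no level for the tests under Data analysis.

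**5. Illustration of the freedom left open.** Assume 5% two-sided per test, all nulls true, two outcomes (HbA1c, blood pressure), four times and one comparator: 2 × 4 = 8 tests.

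- Independent: 1 − 0.95⁸ = 0.337.
- Equal correlation 0.5 (simulation, 200,000 draws): 0.251.
- Equal correlation 0.8 (same simulation): 0.157.
- Results in PEP's favour only: 1 − 0.975⁸ = 0.183 if independent, 0.126 at correlation 0.5 and 0.078 at 0.8, against a nominal 0.025.

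The correlations and the 5% per test are assumptions; the protocol gives neither.

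**The case against.** The strongest reply is that this is an audit of many indicators against standards, and that its parts have different purposes. The Abstract and Subjects assign programme impact to the participant versus non-participant cohort, and the Abstract ties the paired tests to each audit cycle. On that reading the comparator is implied. This carries weight: it shows which contrast the authors most likely meant, and the fix follows it. But neither the hypotheses nor Data analysis says so, and item 2 stands there on equal terms.

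It can also be said that an abstract abbreviates and that item 2 is a drafting slip. Both are plausible. Yet the Abstract states what the primary outcomes are, with no hint that the list is partial. Annual repetition of the audit cycle and follow-up of the cohort to September 2015 might in practice supply other times, but the extraction form does not list them.

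A reader might go further and infer that every test runs at full alpha, that any one favourable result would count as proof, or that 24 tests are in play (three outcomes, four times, two contrasts). The protocol supports none of these. It states no alpha for the analyses and no success rule, and a multiplicity rule may sit in a statistical analysis plan that is not shown. The count of 24 gives 10-year CVD risk four time points, although hypothesis 4 speaks only of the longer term, and it attaches the hypotheses' times to item 2, which lists others.

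**Conclusion.** The point holds as an internal contradiction: three primary outcomes against five, no comparator in hypotheses 2 and 3, and a paired-test schedule that matches the clinical extraction schedule at only two of its four follow-up times (12 and 36 months). These conflicts are in the protocol itself and do not depend on what an analysis plan might add.

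The absence of a multiplicity rule is not part of the finding. The range of about 16% to 34% shows what the open choice could cost if each of eight tests were run at 5%; it is not the error rate of a stated analysis.

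The between-group contrast is the better basis for a claim of effectiveness because it removes a shared secular trend and, if the groups start at similar levels, regression to the mean. It does not remove confounding from who chose to take part.

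**What to change.** 1. Make the Abstract's primary list match the one under Outcome measures.
2. In Data analysis item 2, separate clinical outcomes (12, 24, 36 and 48 months, as in Hypotheses and Appendix C) from patient-reported outcomes (6, 12, 36 and 60 months), and correct the Abstract's 6 and 12 months to match. Appendix C lists patient-reported items at 0 and 6 months only, so align that row in the same edit.
3. State in Hypotheses and Data analysis that effectiveness on HbA1c below 7% and on the blood pressure target is judged by the PEP versus non-participant difference in change from baseline in the DM cohort described under Subjects, with 12 months as the primary time. Limit the blood pressure contrast to DM patients unless a comparator for HT patients is named, because that cohort contains DM patients only.
4. Label before-after tests, cycle-versus-cycle tests and later times as supportive. Report structure and process descriptively against the set standards.

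No particular testing order between HbA1c and blood pressure is required; how the two combine can be set in the analysis plan.

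**Cost.** Mostly wording, and no added patients. Three things go beyond wording. Non-participants need an index date for baseline, since the cohort is fixed on one calendar date. A difference in change in proportions needs more than the single-time chi-square test of item 3. Before-after results and later times can no longer carry the headline claim.

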**Secondary**

- Clinical outcomes including LDL and BMI.
- Cardiovascular complications.
- Renal complications.
- Patient reported outcomes (PRO) measured by the change in SF-12v2 scores, the PEI and GRS scores at 6, 12, 36 and 60 months, and change in patient’s knowledge on disease at 12 months.
- GOPC consultation, SOPC, A&E and hospital attendance rates in the past 12 months; the audit cycle will be repeated annually over a period of 5 years.

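### Hypothesis 6 claims no increase in service use, but the protocol names only difference tests, with no comparator and no largest acceptable increase

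*Protocol*

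**What the plan says.** The Hypotheses section opens with "The following hypotheses will be tested". Item 6 is that participants "should not have any increase in service utilization rates". It does not say whether the increase is measured against the patients' own baseline or against non-participants, and it allows no tolerance.

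The service outcomes listed under Outcome measures (Secondary) are "GOPC consultation, SOPC, A&E and hospital attendance rates in the past 12 months". Private service use is collected separately, in the telephone survey.

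The Data analysis section names these tests for service outcomes:

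- Item 2: within-patient changes up to month 60, service outcomes among them, "will be compared by paired sample t-test". This is a before-after comparison without controls.
- Item 3: an independent t-test or chi-square test "will be used to compare the clinical and service utilization outcomes between PEP patients and controls".
- Item 4: the same two tests between audit cycles.

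The only sample size in the protocol is for quality of life. The record-based comparison uses every eligible diabetic patient in HA general outpatient clinics on a fixed date. The number of such patients is not given.

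**The concern.** Hypotheses 2 to 5 predict improvement, so a significant difference in the right direction supports them. Hypothesis 6 predicts the absence of a harmful change. A test whose null hypothesis is equality cannot support that: a non-significant result may reflect a true zero or too little information, and a significant one may reflect an increase too small to matter.

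Two further gaps follow from the same text. First, the before-after test and the between-group test could disagree, and nothing says which one decides. Second, the before-after comparison runs to 60 months without controls, so it cannot separate the programme from changes over time such as ageing or disease progression.

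The results are meant to guide policy. For that, the HA needs to know how large an increase the data exclude, and the named tests do not report it.

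**Working it through.** The documents give no SD or margin for service use, so increases are in SD units. Tests are two-sided at 5% with equal groups, using the normal approximation.

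**The plan's own figure.** Inputs from Sample size calculation: effect 0.3 SD, 80% power, 25% loss at each of four follow-ups.

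- n per group = 2 × (1.96 + 0.8416)² / 0.3² = 174.4, so 175 per group and 350 in total, as stated.
- 175 / 0.75⁴ = 553.1, against 550 stated, which is close. Conversely, 550 × 0.75⁴ = 174.0 per arm remain after four losses.

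That arithmetic is sound, but it was done for quality of life, not for hypothesis 6.

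**Telephone survey (private use, if it falls under hypothesis 6).** Non-centrality = d × √(n/2).

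- 174 per arm: 95% CI half-width = 1.96 × √(2/174) = 0.21 SD. For d = 0.10, non-centrality = 0.1 × √87 = 0.93 and power is about 15%, so a true rise is non-significant about 85% of the time.
- 550 per arm (no losses): non-centrality = 0.1 × √275 = 1.66 and power is about 38%, so it is non-significant about 62% of the time. At d = 0.20 the figure falls to 9%.

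**HA-record cohort (size assumed).** Smallest significant observed difference = 1.96 × √(2/n).

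| n per group (assumed) | Smallest significant observed difference | Chance that a true rise of 0.02 SD is significant |
| --- | --- | --- |
| 5,000 | 0.039 SD | 17% (non-centrality 1.0) |
| 20,000 | 0.020 SD | 52% (non-centrality 2.0) |
| 100,000 | 0.009 SD | over 99% (non-centrality 4.5) |

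The same true rise of 0.02 SD is thus usually missed at one plausible cohort size and almost always flagged at another. No statement about what size of rise matters enters either result.

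**What a margin would require (margins are illustrative).** n per group = 2 × (1.96 + 0.8416)² / margin², for one-sided 2.5%, 80% power and a true difference of zero: 6,280 at 0.05 SD, 1,570 at 0.10 SD, 393 at 0.20 SD and 175 at 0.30 SD. A large record cohort could support a tight margin; 175 survey patients per arm could support only a wide one.

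**The case against.** **No decision rule is stated.** The protocol never says that a non-significant test upholds hypothesis 6 or that a significant one refutes it, and margins are often left to an analysis plan. A reader might infer that the protocol adopts that rule, and the text does not support this. What stands is narrower: the protocol itself chose and named the tests, and they do not fit its own hypothesis.

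**The audit framework could supply a standard.** Methods promises a criterion and target for each indicator, and service utilization is among the outcome indicators. An acceptable level could be set there. But the framework is still to be developed, Data analysis does not tie these tests to it, and a target does not turn a difference test into evidence of no increase.

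**The survey figures are a pessimistic case.** The 174 per arm applies at month 60. The Abstract and Subjects sections speak of 550 and 550 for each cluster, so pooling over clusters would lower the miss rates. Private use is also absent from the listed service outcomes. Both points are correct, which is why the survey figures are conditional.

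**The cohort figures are assumed.** A reader might infer that trivial differences are bound to be significant in the record cohort. At 20,000 per group a true 0.02 SD rise is significant only about half the time, so that certainty is not warranted.

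**Cost-effectiveness.** A reader might also infer that a wrong verdict on hypothesis 6 would carry into the cost-effectiveness model. The inputs named in Data analysis item 5 are cost, clinical, quality-of-life and private-use cost data, not that verdict.

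**The before-after comparison.** A rise over time would count against hypothesis 6 rather than falsely confirm it, and item 3 already plans a controlled comparison. The protocol does not claim that the paired test shows causation. What remains is that the uncontrolled test should not decide this hypothesis.

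**Conclusion.** The concern holds in this form: a declared hypothesis of no increase is paired with tests of difference, without a comparator, a margin or a stated decision rule. Because no other rule is given, the conclusion would depend heavily on the number of patients analysed. That structural point needs no assumption.

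The sizes do rest on assumptions. The survey miss rates (85% and 62% for a true 0.10 SD rise) assume that private use counts and that one set of 550 per arm is analysed. The cohort figures assume group sizes of 5,000 to 100,000.

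This concerns secondary outcomes and leaves the sample size arithmetic intact. It should be corrected because the claim is listed for testing and the correction is cheap.

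**What to change.** Amend hypothesis 6 and Data analysis items 2 and 3:

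- Name non-participants as the comparator for hypothesis 6.
- For each service type (GOPC, SOPC, A&E, hospital), report the PEP-versus-control difference or rate ratio with its two-sided 95% CI. State whether private use is included.
- Conclude no increase only if the upper limit lies below a margin that the HA and the investigators fix before data extraction, for example within the quality-of-care framework. Otherwise report an increase or an inconclusive result. The documents supply no margin, so none is proposed here.
- Keep the paired before-after comparison descriptive for this hypothesis.

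A count model adjusted for prior-year use is a reasonable option but is not needed for this correction.

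The cost is a change of analysis wording and agreement on a margin for each service. No new data or patients are needed. The downside is that some services, particularly any analysed only in the survey, may come out as inconclusive.
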